## Abstract

**Background:**

Glenohumeral subluxation (GHS) is a common complication following stroke, with an incidence rate of up to 73% in the acute phase, significantly impairing upper limb functional recovery and activities of daily living. Conventional support devices, such as the Harris hemiplegic sling and Bobath sling, have limitations including tendency to slip and displacement, resulting in incomplete reduction. To address these challenges, our research team has developed a novel 3D-printed elbow-forearm support orthotic device.

**Methods:**

This study employs a single-center, prospective, assessor-blinded randomized controlled trial design. We plan to recruit 60 post-stroke patients with GHS, who will be randomly allocated to either the intervention group (elbow-forearm support orthosis) or the control group (conventional shoulder sling). The intervention period is 4 weeks with 6 h of daily wear, followed by an 8-week follow-up period (total observation period of 12 weeks). The primary outcome measures are vertical distance (VD) and horizontal distance (HD) from the inferior margin of the acromion to the center of the humeral head. Secondary outcome measures include the Modified Ashworth Scale, Visual Analog Scale for pain, Fugl-Meyer Assessment for upper extremity motor function, and Modified Barthel Index. Statistical analysis will be performed using mixed-effects linear models.

**Discussion:**

The elbow-forearm support orthosis improves GHS through mechanisms including biomechanical support and neuromuscular modulation. This study employs standardized radiographic measurements, multidimensional assessment systems, and rigorous randomization design, which may provide high-quality evidence-based medicine for the treatment of post-stroke GHS. Study limitations include single-center design and limited sample size, necessitating multicenter large-scale studies for validation.

**Clinical trial registration:**

https://www.chictr.org.cn/, identifier ChiCTR1800018730.

## Introduction

Stroke is one of the leading causes of adult disability worldwide, with approximately 13.7 million new cases annually (1). Glenohumeral subluxation (GHS), a common complication following stroke, occurs in up to 73% of patients during the acute phase, with symptoms deteriorating over time in 67% of affected individuals (2). GHS not only reduces proprioception in the affected limb and exacerbates shoulder pain but also significantly restricts shoulder range of motion, ultimately impairing upper limb functional recovery and activities of daily living (3).

Current clinical approaches for managing GHS include functional electrical stimulation (4), kinesiotaping (5), and shoulder orthoses (6). However, meta-analysis results indicate that these conventional therapeutic techniques demonstrate suboptimal efficacy in improving post-stroke GHS (7). Notably, the only intervention recommended by the American Stroke Rehabilitation Guidelines is maintaining comfortable upper limb positioning and using supportive devices, though this recommendation carries a low level of recommendation and evidence quality (Class IIa recommendation; Level C evidence) (8).

Conventional support devices, such as the Harris hemiplegic sling and Bobath sling, while providing some immediate benefits, have significant limitations: these devices tend to slip due to gravitational forces, are prone to displacement during movement, can only achieve vertical reduction without anterior–posterior repositioning, and demonstrate incomplete overall reduction effects (9, 10). To address these challenges, our team has developed an innovative elbow-forearm support orthosis using 3D printing technology (Chinese Patent No.: CN201810839207.6). Preliminary studies demonstrate that this device significantly outperforms traditional traction-type orthoses in terms of immediate reduction effectiveness and user satisfaction (11).

The elbow-forearm support orthosis is theorized to function through the following mechanistic pathway: (1) Structural alignment phase: The adjustable waist fixation belt and elbow joint positioning device maintain humeral head alignment relative to the acromion, reducing the vertical and horizontal displacement characteristic of GHS; (2) Neuromuscular optimization phase: By maintaining optimal alignment, the device reduces abnormal traction forces on soft tissues, decreasing nociceptive input and allowing normalization of muscle tone through reduced protective muscle guarding; (3) Functional recovery phase: With improved alignment and reduced pain-driven inhibition, the affected rotator cuff muscles are positioned to engage more effectively during rehabilitation, facilitating sensorimotor integration and motor learning. This three-stage model grounds our outcome measurement strategy, where vertical distance (VD)/horizontal distance (HD) serve as objective biomarkers of the mechanical intervention, while spasticity and pain measures reflect the neuromuscular consequences of improved alignment, and motor/functional measures capture the downstream clinical benefits.

As a specialized neurorehabilitation center, the Department of Rehabilitation Medicine at Guangdong Sanjiu Brain Hospital treats a large volume of stroke patients annually and has accumulated extensive experience in rehabilitation therapy and orthotic applications. Based on our preliminary research findings and clinical practice requirements, we plan to conduct a randomized controlled trial to systematically evaluate the therapeutic efficacy of the elbow-forearm support orthosis for GHS in stroke patients.

## Study design and methods

This study employs a single-center, prospective, assessor-blinded randomized controlled trial design and will be conducted at the Department of Rehabilitation Medicine, Guangdong Sanjiu Brain Hospital, with a study duration of 12 months. The study protocol has been registered with the Chinese Clinical Trial Registry (ChiCTR1800018730) and approved by the Ethics Committee of Guangdong Sanjiu Brain Hospital [Ethics Approval No. 2018 (02)].

The research study will adhere to the CONSORT (Consolidated Standards of Reporting Trials) Statement. The study protocol follows the SPIRIT (Standard Protocol Items: Recommendations for Interventional Trials) 2013 Statement (S1 Checklist). The flow diagram of study is shown in Figure 1. The schedule of enrollment, interventions, and assessments is described in Table 1.

**Figure 1 fig1:**
[figure not shown]
Study design (randomized controlled trials) and assessment time points (CONSORT chart).

**Table 1 tab1:** Schedule of enrolment, interventions, and assessments.

Item	Study period				
	Screening	Baseline	Treatment	Follow-up	
Timepoint	-1 week	0	4-weeks	8-weeks	12-weeks
Enrolment					
Eligibility screen	×				
Signed informed consent	×				
Randomization		×			
Interventions					
Intervention group		×	×		
Control group		×	×		
Assessments					
Primary outcome					
VD		×	×	×	×
HD		×	×	×	×
Secondary outcomes					
MAS		×	×	×	×
VAS		×	×	×	×
FMA-UE		×	×	×	×
MBI		×	×	×	×
Adverse Events		×	×	×	×

**×**Represents data collection timepoint. VD, Vertical distance; HD, Horizontal distance; MAS, Modified Ashworth Scale; VAS, Visual Analog Scale; FMA-UE, Fugl-Meyer Assessment of Upper Extremity function; MBI, Modified Barthel Index.

To ensure the scientific rigor and feasibility of randomization, this study employs computer-assisted stratified randomization using the Research Electronic Data Capture (REDCap) system. Stratification factors include age (≤50 years or >50 years) and time since stroke onset (≤30 days or >30 days). An independent biostatistician, who is not involved in patient enrollment, outcome assessment, or data analysis, will generate the randomization sequence using the minimization algorithm in SAS 9.4 software. The sequence will be encrypted and stored in a password-protected database accessible only to authorized personnel. The REDCap randomization system is independently managed by the hospital’s Information Technology Department, ensuring that research team members cannot access the randomization algorithm or modify the sequence. Group assignment information is automatically generated by the system upon completion of baseline assessment and baseline eligibility confirmation. Research coordinators responsible for patient enrollment, informed consent, and baseline assessments are blinded to future group allocations and do not have access to the randomization system until after baseline assessments are complete and all eligibility criteria are verified. Given the distinctive characteristics of the intervention devices, an assessor-blinded design will be implemented: all outcome measure assessments will be conducted by independent assessors who have received standardized training, do not participate in the treatment process, and remain blinded to patient group assignments. Additionally, patients will be explicitly instructed not to disclose their treatment group allocation during the assessment process. The effectiveness of allocation concealment will be assessed by comparing baseline characteristics between groups using chi-square test (categorical variables) and independent samples *t*-test (continuous variables). Significant imbalance in baseline characteristics would suggest inadequate allocation concealment.

This study comprises two parallel groups: the intervention group (elbow-forearm support orthosis) and the control group (conventional shoulder sling). During the 4-week intervention period, patients in both groups will use their respective devices regularly for 6 h daily while simultaneously receiving standard rehabilitation therapy according to current clinical guidelines. To ensure standardized intervention implementation, all healthcare personnel involved in treatment will receive systematic training in device usage and monitoring protocols. Following the completion of the 4-week intervention, an 8-week follow-up period will be conducted, during which patients will maintain daily rehabilitation diaries.

This study has established a rigorous quality control system to ensure data quality and trial integrity. All research procedures will be strictly executed according to standard operating procedures, with independent clinical research assistants conducting regular monitoring visits to verify protocol compliance and data accuracy. Trial data will be collected through electronic case report forms within the REDCap system, which incorporates built-in data range checks and validation rules to effectively ensure data quality. Additionally, a comprehensive adverse event recording and assessment mechanism has been established.

Outcome measure assessments will be conducted at baseline, and at 4, 8, and 12 weeks post-randomization. Primary outcome measures will employ standardized imaging techniques to measure VD and HD from the inferior margin of the acromion to the center of the humeral head. All imaging measurements will be performed by independent radiologists who are blinded to group allocation, ensuring objectivity and reliability of assessment results.

### Study participants

This study will recruit post-stroke patients with GHS from the Department of Rehabilitation Medicine at Guangdong Sanjiu Brain Hospital. All participants must meet the following criteria and provide informed consent.

#### Inclusion criteria

First-ever stroke (cerebral infarction or intracerebral hemorrhage confirmed by imaging); time from stroke onset to enrollment ≤6 months; age 18–80 years; GHS confirmed by imaging; Modified Ashworth Scale score ≤3; Mini-Mental State Examination (MMSE) score ≥21 with ability to understand and cooperate with treatment; stable vital signs with indications for rehabilitation therapy.

#### Exclusion criteria

Organic pathology around the shoulder joint (fracture, dislocation, arthritis, etc.); history of previous shoulder surgery or severe trauma; contraindications to rehabilitation therapy (severe cardiopulmonary dysfunction, coagulation disorders, etc.); severe cognitive impairment or psychiatric disorders; unsuitability for orthotic device wear (skin lesions, allergic history, etc.); receipt of treatments affecting muscle tone within the past 4 weeks (botulinum toxin injection, nerve block, etc.); participation in other clinical trials that may interfere with assessment.

The research team will conduct systematic screening of potential participants. Eligible candidates will receive a participant information sheet, and research personnel will provide detailed answers to any questions. The informed consent process will be completed after a minimum 24-h consideration period. All research personnel will undergo uniform training and strictly adhere to standardized screening and informed consent procedures.

### Sample size calculation

The sample size calculation for this study is based on the primary outcome measures of VD and HD from the inferior margin of the acromion to the center of the humeral head. According to Kumar et al. (12), the expected difference for VD is 5.2 ± 6.8 mm, and for HD is 4.8 ± 6.2 mm. Since the sample size calculation based on VD difference yields a larger result, we chose to base our sample size estimation on VD.

With a two-sided significance level of *α* = 0.05 and power (1-*β*) = 0.80, we employed the sample size calculation formula for independent samples t-test. Calculations were performed using PASS software (version 15.0, NCSS, LLC., Kaysville, Utah, United States) (13). Based on the systematic review by Nadler et al. (6), similar studies with 6–12 week follow-up periods report dropout rates of 15–25%. Considering that this is a single-center study with a 12-week follow-up period, we adopted a relatively conservative estimate and set the dropout rate at 20%.

Based on these parameters, the minimum required sample size is 25 participants per group. Accounting for a 20% dropout rate, we determined to recruit 30 participants per group, for a total sample size of 60 participants. The recruitment period is anticipated to last 6 months; if the planned sample size is not achieved, the recruitment period will be appropriately extended. We acknowledge that our sample size calculation, while based on the conservative.

endpoint-only t-test approach, will be analyzed using mixed-effects linear models that leverage repeated measures and within-subject correlations. This mismatch is intentional and conservative: mixed models typically provide greater statistical power than endpoint-only comparisons. Thus, our sample size of *N* = 60 represents a conservative estimate and ensures adequate power across analysis approaches.

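### The sample size does not reproduce: the stated inputs need 28 per group, not 25, and 30 recruited with 20% dropout leaves 24, so t-test power is about 74%, not 80%

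*Protocol article*

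**What the plan says.** All of the relevant text is in the protocol article, Sample size calculation.

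- Effect sizes, taken from a cited study: "the expected difference for VD is 5.2 ± 6.8 mm, and for HD is 4.8 ± 6.2 mm".
- Sizing outcome: "we chose to base our sample size estimation on VD", on the ground that VD gives the larger number.
- Error rates: "With a two-sided significance level of *α* = 0.05 and power (1-*β*) = 0.80".
- Method: "we employed the sample size calculation formula for independent samples t-test", run in PASS 15.0.
- Dropout: 20%, chosen from a quoted range of 15–25% in similar studies.
- Result: "the minimum required sample size is 25 participants per group. Accounting for a 20% dropout rate, we determined to recruit 30 participants per group", 60 in total.

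The section then notes that the analysis will use mixed-effects models rather than an endpoint t-test. It calls this mismatch intentional and conservative, and says that N = 60 "ensures adequate power across analysis approaches".

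**The concern.** The section gives every input that a two-sample t-test calculation needs, so the result can be checked directly, and 25 per group looks too small for a standardised difference of about 0.76. The dropout step also looks wrong on its face: 20% of 30 is 6, which leaves fewer than the 25 just declared to be the minimum. Both slips push power in the same direction.

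This calculation is the only justification offered for N = 60. If the real power is below 80% while the text describes the size as conservative, a reader of a non-significant result may give it more weight as evidence of no effect than the design supports.

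**Working it through.** **Inputs (all from Sample size calculation).** VD difference 5.2 mm, SD 6.8 mm; HD difference 4.8 mm, SD 6.2 mm; two-sided alpha 0.05; power 0.80; equal allocation; 20% dropout. The figure after ± is read as the common between-patient SD, the only reading that the stated t-test can use.

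**Standardised differences.** VD: 5.2/6.8 = 0.765. HD: 4.8/6.2 = 0.774.

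**Step 1: try to reproduce 25 per group.**

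Normal approximation, n = 2(1.960 + 0.842)²/d²:
- VD: 26.84, so 27.
- HD: 26.19, so 27.

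Exact t-test: noncentral t with 2n − 2 degrees of freedom and noncentrality d√(n/2):

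| n per group | VD power | HD power |
|---|---|---|
| 24 | 73.7% | 74.7% |
| 25 | 75.5% | 76.5% |
| 27 | 78.7% | 79.7% |
| 28 | 80.2% | 81.2% |
| 30 | 83.0% | 83.9% |

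The named method therefore needs 28 per group for either outcome. VD exceeds HD only before rounding.

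Other readings do not give 25 for VD either:
- one-sided test: 22;
- alpha halved to 0.025 for two primary outcomes: 34 by t-test, 33 by the normal approximation;
- one-sample or paired formula: about 14.

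To obtain 25 from the two-sided t-test with a 5.2 mm difference, the SD would have to be about 6.3–6.4 mm, which the protocol does not state.

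**Step 2: the dropout allowance.**
- What was done: 25 × 1.20 = 30.
- What 20% loss requires: 25/(1 − 0.20) = 31.25, so 32.
- What 30 recruits leave: 30 × 0.80 = 24, one below the protocol's own minimum.

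This error is separate from Step 1 and remains even if 25 is accepted.

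**Step 3: both together.**
- Power at 24 evaluable per group: 73.7% (VD), 74.7% (HD).
- Across the protocol's quoted 15–25% dropout range, 25.5 to 22.5 per group: about 76% down to 71% for VD.
- Size on the stated inputs: 28/0.80 = 35 per group, 70 in total, against 60 planned.
- Smallest standardised difference with 80% power at 24 per group: 0.826, and 0.826 × 6.8 = 5.6 mm, not 5.2 mm.

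**Step 4: does baseline adjustment close the gap?** Suppose 6.8 mm is the unadjusted follow-up SD and ρ is the baseline–follow-up correlation. The residual SD is then 6.8√(1 − ρ²). With 24 per group:

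| ρ (assumed) | VD power |
|---|---|
| 0.3 | 77.6% |
| 0.4 | 80.8% |
| 0.5 | 85.0% |

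Power reaches 80% at ρ of about 0.38. The protocol gives no value for ρ.

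**The case against.** The best defence is that 74% describes an endpoint t-test on completers, which is not the planned primary analysis. The Statistical analysis section specifies intention-to-treat, a baseline-adjusted mixed model over repeated visits, and multiple imputation. Someone lost after week 4 still contributes data, so 24 is the low end of the effective sample size. With no losses, 30 per group gives 83.0% even by the plain t-test. A moderate correlation between repeated radiographic distances in the same shoulder is plausible and would restore 80%. It can also be said that the cited source is not visible here, that ± 6.8 might not be a follow-up SD, and that the slip biases no estimate and does not affect type I error.

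Much of this is fair. It means the trial has not been shown to be underpowered for its actual analysis, and the 74% must be labelled as t-test power at 24 completers per group. But it does not rescue the section. The protocol attributes 25 to the t-test, so the mixed model cannot explain that number. The dropout step contradicts the protocol's own minimum without any outside assumption. The assurance of adequate power rests on a general remark about mixed models, with no correlation and no power figure behind it. If a different SD was entered in PASS, the stated input is wrong instead of the result, and the section still needs correcting. The Discussion does list limited sample size as a limitation, which makes an over-reading of a null result less likely but leaves the power statement wrong.

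**Conclusion.** The point holds. On the protocol's own inputs and named method, the minimum is 28 per group rather than 25. After the stated 20% dropout, 30 recruited per group leaves 24, with 73.7% power for VD and 74.7% for HD instead of 80%; for VD the type II error is about 26% rather than 20%. Against a correctly inflated 70, the planned total is short by 10.

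This assumes that 6.8 mm is the common between-patient SD and that the comparison is the endpoint t-test on completers. Under the planned baseline-adjusted model, 80% may be reached, but only with a correlation of about 0.38 or more and with 6.8 mm as an unadjusted follow-up SD. Neither is stated, so describing N = 60 as conservative and adequate for every analysis approach is unsupported; for the t-test under the protocol's own dropout rate it is false.

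**What to change.** Check the figures entered in PASS against those printed, then rewrite the section in one of these ways:

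1. Correct the size to 28 evaluable and 35 recruited per group (70 in total).
2. Keep N = 60 and restate what it delivers by t-test with 24 evaluable per group: about 74% power for 5.2 mm, or 80% power for about 5.6 mm.
3. Keep N = 60 and give the baseline-adjusted power, with the assumed correlation, its source and the meaning of the 6.8 mm SD written down (at 24 per group: about 78% at 0.3, 81% at 0.4, 85% at 0.5).

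In every case, compute the dropout allowance by dividing by 0.80, and remove the statement that N = 60 is conservative and ensures adequate power. Under option 3 a quantified statement can replace it.

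Options 2 and 3 cost a rewording of one section and no extra patients. Option 1 costs 10 more recruits and is not required to put the error right.

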### Interventions

Both groups will receive standardized basic rehabilitation therapy protocols. During inpatient rehabilitation, both groups will uniformly implement a standardized rehabilitation protocol consisting of: 40 min/day of motor therapy (progressing through shoulder range of motion, scapular stabilization, grip/upper limb function, and functional task training, with advancement upon achieving ≥80% movement accuracy and pain VAS ≤ 4); 30 min/day of occupational therapy (standardized upper limb ADL training progressing from dependent to supervised to independent); and 20 min/day of electrical stimulation (10 Hz low-frequency pulses, pulse width 200 μs, biphasic square waveform; applied to the supraspinatus and posterior deltoid, adjusted to visible muscle contraction without pain.). All rehabilitation treatments will be implemented by a team of therapists who have received uniform training.

The intervention group will use a 3D-printed elbow-forearm support orthotic device developed by our research team in addition to routine care. The core structure of the device implements the alignment mechanism through three coordinated components: (1) the adjustable waist fixation belt (circumference adjustable from 60 to 120 cm) provides stable proximal fixation, counteracting gravitational downward translation of the humeral head; (2) the forearm support (length adjustable from 20 to 30 cm) provides lateral restraint at the forearm, limiting the inferior migration and anterior slippage common with conventional slings; (3) the elbow joint positioning device (angle adjustable from 0 to 90°) maintains the scapulohumeral relationship by preventing excessive scapular downward rotation and anterior tilting, which are biomechanical contributors to GHS. Together, these features maintain the humeral head centered beneath the acromion, the primary target of our primary outcome measures. To ensure reproducibility, a standardized fitting and adjustment protocol was established: (1) patient waist circumference and forearm length were measured and recorded prior to initial fitting; (2) belt tightness was deemed adequate when two fingers could be inserted beneath the belt without allowing easy slippage; (3) the forearm support length was adjusted to match the patient’s forearm length; and (4) palpation assessment of the humeral head position relative to the acromion was performed immediately after initial donning. The effect of wearing the elbow forearm brace is shown in Figure 2. The control group will use conventional traction-type traditional shoulder slings routinely used in clinical practice.

